# AIMS AND OBJECTIVES

We aim to assess the feasibility and acceptability of conducting an RCT to compare receiving ABC (an online-delivered, CBT, group-based, body image programme) alongside a psychoeducational body image booklet for women treated for breast cancer, with receiving the booklet only. Results will inform the design, management, and future delivery of an evaluation to assess effectiveness and cost-effectiveness in a definitive RCT.

Specific objectives are to:

- Establish appropriate, inclusive, and acceptable methods of participant recruitment, retention, and management procedures.
- Establish the feasibility and acceptability of quantitative data collection, including determining appropriate primary and secondary outcome measures.
- Adapt and test a measure of health and social care service use, to inform a future economic evaluation.
- Establish intervention adherence and acceptability (of online setting) among participants and ABC facilitators.

This study will examine uncertainties that need addressing before a definitive RCT:

- Recruitment processes and response rates: Responses from potential participants invited for randomisation and investigating reasons for declining.
- Intervention adherence and retention within the study: Percentage of participants completing each ABC session, reading the Macmillan booklet (in the control arm), and completing outcome measures at each assessment. This will additionally help calculate the sample size for the proposed follow-on RCT.
- Participants’ experience of randomisation to either the intervention or control arm and their experience of being in these arms.
- Participants’ responses and feedback to self-complete measures. This will determine suitability of the measures for an RCT.
- Adaptation and testing of a measure of health and social care service use: Assessment of comprehensiveness of the service use measure and acceptability of the measure to collect data for a health economic evaluation.

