We will collect a variety of different type of data exploring acceptability and feasibility. This will inform the design of a future definitive RCT and help refine intervention, recruitment, and retention procedures. Figure 1 provides an outline of participant flow in the study and Table 1 provides an outline of the different assessments and their associated timepoints.

- - 1. **Quantitative measures of feasibility and acceptability**

We will collect the following quantitative data to assess feasibility and acceptability of the research design and ABC:

- - - 1. **Monitoring data**
- Rates of recruitment (and associated response rates), with attention to the method by which women were recruited and their demographic diversity.
- Rates of retention following randomisation:
  - Proportion completing ABC (number of sessions attended and between-session activities completed)
  - Proportion of control arm reading the Macmillan body image booklet (plus percentage of booklet read)
  - Proportion completing outcome measures at each assessment (plus data completeness rates; outcome measures described in 5.6.3).
    - 1. **Self-report rating scales included in outcome assessments (see 5.6.3)**
- Rating scales to explore acceptability of ABC (e.g., the group format, online nature, between-session activities; Appendix 9) - to be completed by ABC participants in the immediate post-intervention assessment, i.e., Week 9.
- A single rating scale examining how helpful participants found the ABC programme will also be included in the three- and six-month follow up assessments (see Appendix 31). This will allow monitoring of how participants’ perceptions of the programme and its impacts may develop over time.
- Rating scales to explore acceptability of the research process generally (e.g., information provided about the study, randomisation process, questionnaires; Appendix 10) – to be completed by all participants in the six-month post-intervention assessment i.e., Week 32.
  - 1. **Qualitative measures of feasibility and acceptability**

In addition to the above, we will collect the following qualitative data to assess feasibility and acceptability of the research design and ABC:

- - - 1. **Open-ended questions included in outcome assessments (see 5.6.3)**

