Descriptive analyses (i.e., percentages and confidence intervals) will be conducted on numbers relating to recruitment (including numbers of eligible women who decide not to proceed after reading the PIS) and retention following randomisation, including numbers who complete ABC (i.e., number of sessions attended and between-session activities completed), who read the Macmillan body image booklet (in the control arm; including percentage of booklet read), and who complete self-report outcome measures at each assessment timepoint (including data completeness rates). We will assess the extent of missing data, withdrawals and loss-to-follow-up.

We will report data in line with the Consolidated Standards of Reporting Trials (CONSORT) 2010 Statement showing attrition rates and loss to follow-up.

- - - 1. **Self-report rating scales**

Descriptive analyses (i.e., means, standard deviations, percentages) will be conducted on the ratings scales related to acceptability of ABC (e.g., the group format, online nature, between-session activities; Appendix 9), as well as those related to acceptability of the research process generally (e.g., information provided about the study, randomisation process, questionnaires; Appendix 10).

- - 1. **Analysis of qualitative data**
       1. **Open-ended questions**

The responses to the open-ended questions asking for feedback on ABC (e.g., the group format, online nature, between-session activities; Appendix 9) and the research process generally (e.g., information provided about the study, randomisation process, questionnaires’ Appendix 10) will be analysed in NVivo using thematic analysis (Braun & Clarke 2006). The analytic process of ‘codebook’ thematic analysis will be used (Braun & Clarke 2006, 2022), whereby text will be coded using a priori codes and themes relating to feasibility and acceptability (informed by O’Cathain et al 2015).

- - - 1. **Interviews**

Interviews will be digitally recorded, transcribed verbatim, and analysed in NVivo using thematic analysis (Braun & Clarke 2006). The analytic process of ‘codebook’ thematic analysis will be used (Braun & Clarke 2006, 2022), whereby transcripts will be coded using a priori codes and themes relating to feasibility and acceptability (informed by O’Cathain et al 2015).

- 1. **Analysis of self-report outcome measures**

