| Please select one option: |  |  |  |  |  |

If you did **not read** any of the booklet, could you please tell us why?

________________________________________________________________________________________________________________________________________________

Did you seek any **other support** for your body image during the study?

|  | Yes | No |
| --- | --- | --- |
| Please select one option: |  |  |

If you **did** seek other support, could you please tell us what this was?

________________________________________________________________________________________________________________________________________________

How helpful did you find this support?

|  | Not at all helpful  1 | 2 | 3 | 4 | Very helpful  5 |
| --- | --- | --- | --- | --- | --- |
| Please select one option: |  |  |  |  |  |

If you had been randomly allocated to the **other condition** (either the ABC programme or control group), do you think you would have continued with the study?

|  | Yes | Maybe | No |
| --- | --- | --- | --- |
| Please select one option: |  |  |  |

Could you please tell us why you selected this?

________________________________________________________________________________________________________________________________________________

How have you found the overall experience of **taking part in this study?**

|  | A very negative experience  1 | 2 | 3 | 4 | A very positive experience  5 |
| --- | --- | --- | --- | --- | --- |
| Please select one option: |  |  |  |  |  |

Do you have any other feedback on the whole study, or suggestions for improvement?

____________________________________________________________________________________________________________________________________________________________________________________________________________________________________________________________________________________________________________________________________

_________________________________________________________________________________

_________________________________________________________________________________

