**12.15 Appendix 15: Interview Schedule: Control Participants Finished Study**

For participants who were randomised to the control group and completed the whole study (i.e., completed the last questionnaire).

- First of all, how have you found taking part in this study?
- Did you feel that the information provided about the study was clear?
  - Were you able to understand what taking part would involve?
- How did you find the contact and communication from the research team throughout the study?
  - Was each stage of the research (e.g., each questionnaire) clear?
  - Did you feel comfortable corresponding with them?
- How did you feel about the 50% chance that you would be able to attend the body image programme (i.e., being randomised)?
  - How did you feel when you were told that you would not be attending the body image programme?
  - What made you decide to continue with the study, despite not being allocated to the body image programme?
- What did you think of the Macmillan booklet that you were given?
  - Were you aware of this booklet?
  - Did you read the whole Macmillan booklet?
  - Did you find it helpful/unhelpful? Why?
- Did you access any other form of support in relation to your body image?
  - What was this?
  - Was it helpful/unhelpful? Why?
- How did you find completing the questionnaires throughout the study? *(share the questionnaire to remind them of the questions)*
  - What did you think of the format by which you completed these (either paper or online). How could this be improved?
  - How did you find the time it took to complete each questionnaire?
  - How did you find the instructions for completing the different questions in the questionnaire?
  - Did you feel that the questions that you were asked were relevant?
  - Were there other impacts of your body image concerns that were not explored or asked about in the questionnaires?
- What else could we do to help encourage women to take part in a future study and to stay until the end?
- Do you have anything else to add, or any questions?

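### Appendix 10 has no rating of the randomisation process, although the protocol says it does; across the sample randomisation is captured only by one indirect hypothetical item with a free-text reason

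*Protocol*

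**What the plan says.** Section 2 (Aims and Objectives) lists among the uncertainties to settle before a definitive trial the participants' "experience of randomisation to either the intervention or control arm and their experience of being in these arms". The Trial Summary counts participant feedback on the research process among the primary outcome measures, and Section 7.1 says the primary aims will be met partly through the self-report rating scales.

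Section 5.6.1.2 describes the instrument: "Rating scales to explore acceptability of the research process generally (e.g., information provided about the study, randomisation process, questionnaires; Appendix 10", which is "to be completed by all participants in the six-month post-intervention assessment i.e., Week 32". Section 7.1.1.2 gives the analysis: "Descriptive analyses (i.e., means, standard deviations, percentages) will be conducted on the ratings scales", including those on "acceptability of the research process generally (e.g., information provided about the study, randomisation process, questionnaires; Appendix 10". Sections 5.6.2.1 and 7.1.2.1 describe the open-ended questions on the same form in the same terms.

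Appendix 10 is reproduced in full. Its one closed item on allocation asks about the arm the woman was not in: "either the ABC programme or control group), do you think you would have continued with the study". The answers are Yes, Maybe or No, and the next prompt asks for the reason.

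Direct questions appear elsewhere. The interview schedules for women who finish the study (Appendices 15 and 16) ask how they felt about the 50% chance of attending the programme. Control completers are also asked: "How did you feel when you were told that you would not be attending the body image programme".

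**The concern.** The protocol names a topic, an instrument and an analysis, and the instrument does not carry a rating on that topic. This is a mismatch between the body of the protocol and its own appendix, not a detail that would normally wait for a statistical analysis plan.

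The existing item is a weak substitute. A control who reached Week 32 is asked whether she would have stayed had she been given the programme. Her answer does not show whether she found allocation by chance, or a booklet alone, acceptable. A woman in the ABC arm is asked to guess about an arm she did not experience. That is useful as anticipated continuation, but it is not her experience of being randomised.

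What is at stake is the design of the definitive trial. Whether women seeking help will accept an even chance of a booklet alone bears on the choice of comparator, and Appendix 13 already raises a waitlist control as a possible change. If the other-arm item is reported under the label the protocol gives the form, it could be read as evidence that randomisation was acceptable, which it cannot show for controls.

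**Working it through.** The protocol gives no figure on this point, so the check is a comparison of the form with its description, followed by simple arithmetic on coverage.

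**Items in Appendix 10**

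| Type | Content | On randomisation or allocation |
| --- | --- | --- |
| Numeric rating (7) | clarity of study information; contact and communication; relevance of the questionnaires; how tiring they were; helpfulness of the booklet; helpfulness of other support; overall experience of the study | 0 of 7 |
| Other closed item (4) | prior familiarity with the booklet; how much was read; whether other support was sought; continuation in the other arm | 1 of 4 (hypothetical) |
| Open prompt (5) | expansion of the first answers; why the booklet was not read; what other support; reason for the other-arm answer; any other feedback | 1 of 5 |

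Of the 11 closed items, one concerns allocation. It is categorical and concerns the arm not received. The rating descriptions in 5.6.1.2 and 7.1.1.2 are therefore unmet. The open-question descriptions in 5.6.2.1 and 7.1.2.1 are met in part, through the reason prompt.

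**Interview coverage** (Section 5.6.2.2: 16–20 interviews, about equally spread over six circumstances, one of which is women who never consented)

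- Per circumstance: 16/6 = 2.7 to 20/6 = 3.3, so about 3 control completers.
- Randomised interviewees: 16 × 5/6 = 13.3 to 20 × 5/6 = 16.7, so about 13–17.
- As a share of the planned 120: 13.3/120 = 11.1% to 16.7/120 = 13.9%.
- Appendices 15 and 16 ask about being randomised directly. Appendix 11 (decliners) probes whether randomisation was the reason. Appendices 12 and 13 (drop-outs) probe disappointment with allocation. Appendix 14 checks only that randomisation was understood.

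**Precision of a direct rating, reported as a proportion within the control arm**

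The 95% half-width is 1.96 × √(p(1 − p)/n), which is largest at p = 0.5.

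- n = 60 (all controls return the form): 1.96 × √(0.25/60) = 0.127, or 12.7 points.
- n = 48 (80% return, 0.80 × 60): 1.96 × √(0.25/48) = 0.141, or 14.1 points.

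The 80% is an assumption. It borrows the proportion completing all assessments in the earlier in-person study, given in Section 1; the protocol states no expected return rate for this trial.

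**The case against.** A reader might infer that acceptability of randomisation is not measured in the full sample at all, or that the planned analysis has nothing to summarise. The protocol does not support either reading. The other-arm item and its reason prompt go to all participants at Week 32. Section 7.1.1.2 plans percentages, which suit a three-category answer, and Section 7.1.2.1 plans thematic analysis of the text.

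Other evidence also bears on the question. Section 7.1.1.1 reports eligible women who do not proceed after reading the information sheet, together with withdrawals and loss to follow-up. Section 5.1 collects brief written reasons for declining on the expression of interest form. Appendix 10 asks about helpfulness of the booklet and overall experience. The interviews reach decliners and drop-outs as well as completers. The topics in 7.1.1.2 are introduced as examples, and Section 2 promises no numeric score for the experience of randomisation, so a mainly qualitative assessment would be a legitimate choice.

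A new rating on a follow-up form would also share a limit with the present item: only women still in the study answer it.

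All of this stands, and it narrows the point. It does not remove it. Behavioural data show how many decline or leave, not how those who stay regard their allocation. The interviews give depth from a few women. The rating that the protocol says exists would supply the missing piece, and it is absent.

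**Conclusion.** The point holds in this form: the rating scales are described as covering the randomisation process, and no rating on the form does. Across the sample, randomisation is captured only indirectly, by one hypothetical item and its free-text reason, among women who return the Week 32 form. Questions put directly on randomisation or allocation are confined to 16–20 interviews, about 13–17 of them with randomised women if the six circumstances are equally filled.

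It would go too far to say that a favourable answer among controls is to be expected; no figure in the protocol supports a forecast. What can be said is that, whatever controls answer, the item does not show whether they accepted chance allocation or the booklet-only arm.

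No sample size or comparative analysis depends on this. It still deserves correction, because it concerns a stated uncertainty and a primary outcome of the feasibility study, the remedy is cheap, and the information may not be recoverable once a woman has returned her last form.

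**What to change.** Add one or two direct 1–5 ratings for all women: how acceptable it was to be allocated to a group by chance, and how satisfied she was with the group she was allocated to. Summarise them by arm under Section 7.1.1.2. Ask them at T2 as well as T4 if possible, so that women who leave between the two are included.

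Keep the other-arm item for both arms, but label it in the analysis as anticipated continuation in the other arm, not as acceptability of randomisation. If no rating is added, the least that is needed is to correct the descriptions in 5.6.1.2 and 7.1.1.2 so that they match the form.

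The costs are small but real. The questionnaire becomes slightly longer. Women who completed the form before the change will have no data on the new items. Women who leave before T2 are still missed, and answers come only from those who return a form, so the ratings should be read alongside attrition by arm. Protocol version 3 added short items to the follow-up questionnaires, so the change is practicable. The sponsor should determine the amendment category.
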